## Abstract

**Background:**

Angiotensin receptor neprilysin inhibitor (ARNI) sacubitril‐valsartan has been recommended as one of the first‐line therapies in heart failure with reduced ejection fraction. However, whether ARNI could benefit patients with ST‐segment elevation myocardial infarction (STEMI) by improving left ventricular (LV) remodeling remains unknown. The primary objective of the PERI‐STEMI trial is to assess whether sacubitril‐valsartan is more effective in preventing adverse LV remodeling for patients with STEMI than enalapril.

**Hypothesis:**

We hypothesize that sacubitril/valsartan is superior to enalapril in preventing adverse LV remodeling evaluated by cardiovascular magnetic resonance imaging at the 6‐month follow‐up.

**Methods:**

PERI‐STEMI is an investigator‐initiated, prospective, multi‐center, randomized, open‐label, superiority trial with blinded evaluation of outcomes. A total of 376 first‐time STEMI patients with primary percutaneous coronary intervention (PPCI) within 12 h after symptom onset will be randomized to sacubitril‐valsartan or enalapril treatment. All the patients will receive a baseline cardiovascular magnetic resonance (CMR) examination at 4–7 days post‐PPCI. The primary endpoint is the change of indexed LV mass at the 6‐month follow‐up CMR.

**Results:**

Enrollment of the first patient is planned in November 2021. Recruitment is anticipated to last for 12–18 months and patients will be followed for 5 years after randomization. The study is expected to complete in June 2027.

**Conclusions:**

The results of the PERI‐STEMI trial are expected to provide CMR evidence on whether ARNI could benefit patients with STEMI, so as to facilitate the strategy of CMR‐based risk stratification and therapy selection for these patients. PERI‐STEMI is registered at ClinicalTrials.gov (NCT04912167).

## BACKGROUND

1

Angiotensin receptor neprilysin inhibitor (ARNI) sacubitril‐valsartan, also known as LCZ696, has proven its superiority over enalapril in reducing adverse clinical events in patients with heart failure (HF) and reduced ejection fraction (HFrEF).^1^ Further study showed that treatment with sacubitril‐valsartan compared to valsartan alone is associated with significant improvement in cardiac function and reverse remodeling.^2^, ^3^ Although these benefits for HF with preserved ejection fraction (HFpEF) was not significant, a number of studies have reported that use of sacubitril‐valsartan could result in a lower level of N‐terminal pro‐B‐type natriuretic peptide (NT‐proBNP) and an improvement in left atrial function.^4^, ^5^, ^6^ Given that HF represents a heterogenous group of patients, and a differential treatment effect in this broad population raised by previous data, studies on specific subtype of patients with HFrEF or HFpEF are warranted to recognize the target patients who might benefit most from sacubitril‐valsartan treatment.^5^

Ischemia heart disease (IHD), especially a history of myocardial infarction (MI), is a common etiology of HF.^7^, ^8^ Such patients harbor a high risk of recurrent cardiovascular events and poor prognosis.^9^, ^10^ Early presence and pattern of left ventricular (LV) remodeling were closely associated with the long‐term outcome and should be carefully evaluated.^11^, ^12^, ^13^ Angiotensin‐converting enzyme inhibitors (ACEI) or angiotensin receptor blocker (ARB) are thus suggested for consideration in all MI patients, owing to their additional benefits and protecting mechanism on the heart and vasculature remodeling.^14^, ^15^, ^16^ Sacubitril‐valsartan is efficacious in preventing maladaptive cardiac fibrosis and prevent adverse LV remodeling compared to ACEI treatment.^17^ This superiority has been proven in hypertension, acute HF and MI animal models.^18^, ^19^ Nevertheless, whether it is effective in preventing adverse remodeling, or improving reverse remodeling among patients with ST‐segment elevation MI (STEMI) remains unknown.

Thus, we present the PERI‐STEMI (*P*rospective comparison of *E*arly *R*emodeling *I*maging between ARNI sacubitril/valsartan and ACEI enalapril in *ST*‐*e*levation *m*yocardial *i*nfarction patients) trial. The primary objective of this study is to decide whether sacubitril‐valsartan is more effective in preventing adverse LV remodeling for patients with STEMI, compared to enalapril. We hypothesize that sacubitril/valsartan is superior to enalapril in preventing adverse LV remodeling evaluated by cardiovascular magnetic resonance (CMR) imaging at the 6‐month follow‐up. Secondary objectives include: (a) To examine the long‐term outcome of sacubitril‐valsartan in STEMI, as compared to enalapril; and (b) to explore the capacity of baseline CMR markers in predicting patients who might benefit from treatment of sacubitril–valsartan.

## METHODS

2

### Study design

2.1

This study is an investigator‐initiated, multi‐center, open‐label, parallel‐group, superiority study (Figure 1). Patients will be recruited from approximately 20 hospitals in China. This study has been approved by the ethic committee of West China hospital and all participating centers. PERI‐STEMI is registered at ClinicalTrials.gov (NCT04912167).

**FIGURE 1 clc23744-fig-0001:**
[figure not shown]
Study plan. ACEI, angiotensin‐converting enzyme inhibitors; ARNI, angiotensin receptor neprilysin inhibitor; ECG, electrocardiogram; MACE, major adverse, cardiac event; MRI, magnetic resonance imaging; STEMI, ST‐segment elevation myocardial infarction

### Patient eligibility

2.2

Detailed inclusion and exclusion criteria are presented in Table 1. Briefly, continuous patients aged between 18 and 75 and referred to the designated chest pain center with the diagnosis of spontaneous STEMI will be initially screened. The diagnosis of STEMI will be decided by the physician based on the newest clinical guidelines.^14^, ^20^ Considering that multiple factors may affect ventricular remodeling, this study will only include patients with a uniform baseline condition, namely first‐onset STEMI, successfully treated by primary percutaneous coronary intervention (PPCI) within 12 h after onset, and hemodynamically stable to be eligible for further evaluation. Hemodynamically stable is defined as fulfilling the following criteria: (a) systolic blood pressure (SBP) ≥ 100 mmHg for patients who received ACEI/ARB during the last 24 h or SBP ≥110 mmHg for patients who did not, (b) no increase intravenous treatment with diuretics or vasodilators, and (c) no vasopressors and/or inotropes during the last 24 h prior to randomization.^21^

**TABLE 1 clc23744-tbl-0001:** List of inclusion and exclusion criteria for patients

List of inclusion and exclusion criteria for patients
*Inclusion criteria*
Aged between 18 and 75 years old
First‐time ST‐segment elevation myocardial infarction based on the newest ESC guidelines^a^
Timely primary percutaneous coronary intervention within 12 h from onset^b^
Written informed consent acquired
*Exclusion criteria*
Patients with symptomatic hypotension, or a systematic blood pressure less than 100 mm Hg at screening or 95 mm Hg at randomization.
Patients with Takotsubo cardiomyopathy or myocardial infarction secondary to another medical condition such as anemia, hypotension, or arrhythmia, coronary vasospasm
Known history of or persistent clinical chronic heart failure prior to randomization
Previous use of ARNI, or intolerance or contraindications to study drugs including ARNI or ACEI
History of significant chronic coronary obstruction and adverse ventricular remodeling
History of any cardiomyopathy, valvular heart disease, congenital heart disease, stent or CABG, or planned open‐heart surgery within 3 months
History of hepatic impairment or history of cirrhosis with evidence of portal hypertension
History of chronic renal dysfunction, or eGFR <30 ml/min/1.73 m^2^
History of malignancy and with a life span less than 1 year
Patients with a known history of angioedema related to previous ACEIs/ARB therapy.
With contraindication to MRI examination (pacemaker and claustrophobia) or cannot finish breath‐holding when lying on the examination bed
Pregnancy or nursing women

Abbreviations: ACEI, angiotensin‐converting enzyme; ARB, angiotensin‐receptor blocker; ARNI, angiotensin receptor neprilysin inhibitor; CABG, coronary artery bypass graft; eGFR, estimated glomerular filtration rate; ESC, European Society of Cardiology; MRI, magnetic resonance imaging.

^a^
Including: (a) evidence of myocardial injury (defined as an elevation of cardiac troponin values with at least one value above the 99th percentile upper reference limit) with necrosis in a clinical setting consistent with myocardial ischemia; and (b) ST‐segment elevation in at least two contiguous leads.

^b^
The definition of successful revascularization requires (a) a minimum stenosis diameter reduction to 20% for the culprit vessel; (b) a grade 3 TIMI flow assessed by angiography.

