### Treatment protocol

2.4

Standard peri‐PPCI clinical management will be applied for each participant. The prescriptions of anticoagulants, glycoprotein IIb/IIIa inhibitors, and thrombus aspiration will be left to the physician's discretion. For the patients with multivessel disease (MVD), revascularization of the non‐ischemia related artery is suggested but whether to perform this immediately or in a staged way will be left to the physician's discretion. Subsequently, patients randomized to ARNI group will receive two doses of ARB to ensure a minimum 36‐h washout period prior to initiation of ARNI therapy, and then be started with the first dose or sacubitril‐valsartan, while patients randomized to ACEI group will directly start with the first dose of enalapril. All patients will be monitored for hypotension 6 h after study treatment. In accordance with the current clinical management guidelines, all patients will receive a dual‐antiplatelet drug (aspirin, clopidogrel, or ticagrelor), β‐blocker agent and statins as the standard of post‐STEMI care. The use of sodium‐dependent glucose cotransporter 2 inhibitor (SGLT‐2i) for patients with diabetes will be left to the physician's discretion and recorded.

After initiation of treatment with sacubitril‐valsartan or enalapril, dose of the treatment will be titrated to a target level based on systolic blood pressure of the patients (Table 2). Clinicians are encouraged to uptitrate sacubitril‐valsartan and enalapril to target dose.

**TABLE 2 clc23744-tbl-0002:** Target treatment dose levels based on systolic blood pressure

Dose level	Sacubitril‐valsartan	Enalapril	Systolic blood pressure (SBP)
1	24/26 mg bid	2.5 mg bid	Initial SBP within 100–120 mm Hg and reducing to <100 mg Hg post‐treatment
2	49/51 mg bid	5 mg bid	Initial SBP within 100–120 mm Hg and maintaining ≥110 mm Hg post‐treatment, or Initial SBP ≥120 mm Hg but reducing to <100 mg Hg post‐treatment
3	97/103 mg bid	10 mg bid	Initial SBP ≥120 mm Hg and maintaining ≥110 mm Hg post‐treatment

*Note*: Bid: twice a day.

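### The systolic blood pressure rules for entry differ between section 2.2 and Table 1, and Table 2 assigns no dose level, or two, for some pressures

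*Protocol article*

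**What the plan says.** Three places in the Protocol article set rules by SBP.

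- **Section 2.2, text.** Only haemodynamically stable patients are to be included. The SBP part of that definition has two limits. The first is "systolic blood pressure (SBP) ≥ 100 mmHg for patients who received ACEI/ARB during the last 24 h". The second covers everyone without such treatment in that window, and reads "SBP ≥110 mmHg for patients who did not".
- **Section 2.2, Table 1.** The text gives it precedence in detail: "Detailed inclusion and exclusion criteria are presented in Table 1". Its only SBP item is an exclusion: "Patients with symptomatic hypotension, or a systematic blood pressure less than 100 mm Hg at screening or 95 mm Hg at randomization". It has no 110 mmHg limit, no split by recent ACEI/ARB use and no haemodynamic stability criterion.
- **Section 2.4, Table 2.** After treatment starts, "dose of the treatment will be titrated to a target level based on systolic blood pressure of the patients". The table has three dose levels, each defined by an initial and a post-treatment SBP. Level 1 begins "Initial SBP within 100–120 mm Hg and reducing to <100 mg Hg" and level 3 begins "Initial SBP ≥120 mm Hg and maintaining ≥110 mm Hg". Level 2 covers an initial 100–120 mmHg with at least 110 mmHg after treatment, or an initial SBP of 120 mmHg or more with less than 100 mmHg after treatment.

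Section 2.3 says that eligible patients are then allocated 1:1 through a web-based system, in permuted blocks stratified by centre, and that treatment is open-label. Section 2.9 lists symptomatic hypotension among the safety assessments.

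**The concern.** A site that screens from Table 1 and a site that screens from the text would reach different decisions on the same patient. About 20 hospitals are to recruit, and section 2.2 says it wants a uniform baseline condition. Patients with lower pressures could enter at some sites and not at others, and both study drugs lower blood pressure.

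Table 2 has a separate problem. It is the stated basis for titration, but some ordinary combinations of pressures lead to no dose level and one starting value leads to two. Clinicians must then choose for themselves, and in an open-label trial they do so knowing the arm. Dose intensity and the handling of hypotension may then differ by site or by arm for reasons that the protocol does not set.

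**Working it through.** The plan gives no numerical result to reproduce here. The check is whether the stated intervals agree and whether they cover the range. SBP is taken in whole mmHg.

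**Step 1: the entry rules.** The text admits SBP ≥100 with ACEI/ARB in the last 24 h and ≥110 without. Table 1 admits ≥100 at screening and ≥95 at randomisation. The text does not clearly say at which time point its SBP limits apply, so both are shown.

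| If the text rule applies at | ACEI/ARB in last 24 h | Text admits | Table 1 admits | Passes Table 1, fails text |
|---|---|---|---|---|
| Screening | yes | ≥100 | ≥100 | none |
| Screening | no | ≥110 | ≥100 | 100–109 |
| Randomisation | yes | ≥100 | ≥95 | 95–99 |
| Randomisation | no | ≥110 | ≥95 | 95–109 |

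- Without recent ACEI/ARB, 100–109 mmHg conflicts at both time points. This part needs no assumption on timing.
- The 95–99 mmHg conflict exists only if the text rule applies at randomisation. It then covers all patients. Table 1's 95 mmHg limit could also never act, because the text already requires at least 100 mmHg.

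**Step 2: Table 2 as a decision table.** Each cell gives the level or levels whose conditions are met.

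| Initial SBP | Post-treatment <100 | Post-treatment 100–109 | Post-treatment ≥110 |
|---|---|---|---|
| 95–99 | none | none | none |
| 100–119 | 1 | none | 2 |
| exactly 120 | 1 and 2 | none | 2 and 3 |
| above 120 | 2 | none | 3 |

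- The 100–109 column is empty at every starting pressure.
- The 95–99 row is empty throughout, although Table 1 permits that pressure at randomisation. This assumes that the initial SBP is the one at or near randomisation.
- At exactly 120 mmHg both starting bands apply, so two levels are met.

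**Step 3: is the empty column reachable?** Take a patient with recent ACEI/ARB and an SBP of 105 mmHg. That patient passes both entry rules. If SBP is still 105 mmHg after treatment, no row applies. The gap is therefore reached by a patient who is undisputedly eligible and whose pressure has not changed.

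**The case against.** **The entry rules can be applied together.** The text is an inclusion condition and the Table 1 item is an exclusion, so a patient must pass both. On that reading Table 1 is incomplete rather than in conflict. This is a fair way to run the trial, but the article does not state it. It calls Table 1 the detailed list, and a site using that list alone would enrol patients whom the text rules out.

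**The 95–99 mmHg point depends on timing.** This stands. The reference to randomisation in the stability definition sits with the item on vasopressors and inotropes, and the SBP limits may be meant for screening. A patient at 97 mmHg at randomisation cannot simply be called ineligible by the text.

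**Titration involves judgement, and the overlap at 120 mmHg is a boundary slip.** Clinicians are urged to raise the dose towards target, so some latitude is intended. That does not supply a level for 100–109 mmHg. The overlap is indeed a single value.

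A reader might go further in three ways that the document does not support:

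- *Enrolment could differ by arm.* Eligibility is settled before web-based allocation (section 2.3), so the arm is not known when SBP is judged for entry.
- *Achieved dose confounds the comparison.* Dose reached arises after randomisation and is part of each strategy's effect. The primary analysis in section 2.11 sets no condition on dose.
- *Per-protocol status cannot be assigned.* Section 2.11 leaves protocol deviations to the statistical analysis plan, which is not shown.

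**Conclusion.** The point holds as a conflict between stated rules and a dosing table that cannot be applied as written. It is not a complaint about detail left to another document, since the article prints both tables and their values.

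Certain from the wording:

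- a mismatch between text and Table 1 at 100–109 mmHg without ACEI/ARB in the last 24 h;
- no dose level for a post-treatment SBP of 100–109 mmHg at any starting pressure;
- two levels at an initial SBP of exactly 120 mmHg.

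Conditional:

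- the conflict at 95–99 mmHg, on the text rule applying at randomisation;
- the missing Table 2 row at 95–99 mmHg, on such patients being enrolled as Table 1 allows and on initial SBP meaning the value near randomisation.

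The entry conflict bears on who is enrolled and on their safety, not on the balance between arms. The Table 2 gap arises after allocation, so titration and the handling of hypotension may vary by site or arm. The share of patients affected is not given, and no effect on the primary estimate, type I error or power has been shown.

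**What to change.** The sponsor should reconcile the text of section 2.2, Table 1 and Table 2:

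- State one SBP eligibility rule, with the time point at which it applies and any dependence on recent ACEI/ARB, in identical terms in the text and in Table 1.
- Rewrite the Table 2 bands so that every combination of initial and post-treatment SBP leads to exactly one level, starting from the lowest eligible SBP, and say when the initial SBP is measured.

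The values are for the clinical leads to decide, and none is proposed here. Section 2.6 already has medical treatments recorded at each visit.

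The cost is a protocol clarification, best issued to all sites before the first enrolment. It needs no extra patients or procedures and does not alter the sample size.

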### Randomization and binding procedure

2.3

No run‐in period is included for PERI‐STEMI. Following screening patients who fulfill the eligibility criteria will be randomized (1:1) to either sacubitril–valsartan or enalapril. Permuted block randomization stratified by center will be employed. Randomization will be performed through an Interactive Web‐based Response System, for which a random allocation sequence is created using a standard computerized random‐number generator. This study is an open‐label trial, but the radiologists responsible for imaging analysis will be rigorously blind to the clinical and allocation information.

### Treatment protocol

2.4

Standard peri‐PPCI clinical management will be applied for each participant. The prescriptions of anticoagulants, glycoprotein IIb/IIIa inhibitors, and thrombus aspiration will be left to the physician's discretion. For the patients with multivessel disease (MVD), revascularization of the non‐ischemia related artery is suggested but whether to perform this immediately or in a staged way will be left to the physician's discretion. Subsequently, patients randomized to ARNI group will receive two doses of ARB to ensure a minimum 36‐h washout period prior to initiation of ARNI therapy, and then be started with the first dose or sacubitril‐valsartan, while patients randomized to ACEI group will directly start with the first dose of enalapril. All patients will be monitored for hypotension 6 h after study treatment. In accordance with the current clinical management guidelines, all patients will receive a dual‐antiplatelet drug (aspirin, clopidogrel, or ticagrelor), β‐blocker agent and statins as the standard of post‐STEMI care. The use of sodium‐dependent glucose cotransporter 2 inhibitor (SGLT‐2i) for patients with diabetes will be left to the physician's discretion and recorded.

After initiation of treatment with sacubitril‐valsartan or enalapril, dose of the treatment will be titrated to a target level based on systolic blood pressure of the patients (Table 2). Clinicians are encouraged to uptitrate sacubitril‐valsartan and enalapril to target dose.

**TABLE 2 clc23744-tbl-0002:** Target treatment dose levels based on systolic blood pressure

Dose level	Sacubitril‐valsartan	Enalapril	Systolic blood pressure (SBP)
1	24/26 mg bid	2.5 mg bid	Initial SBP within 100–120 mm Hg and reducing to <100 mg Hg post‐treatment
2	49/51 mg bid	5 mg bid	Initial SBP within 100–120 mm Hg and maintaining ≥110 mm Hg post‐treatment, or Initial SBP ≥120 mm Hg but reducing to <100 mg Hg post‐treatment
3	97/103 mg bid	10 mg bid	Initial SBP ≥120 mm Hg and maintaining ≥110 mm Hg post‐treatment

*Note*: Bid: twice a day.

### Imaging study and analysis

2.5

Image acquisition will be performed twice by qualified cardiac MRI experts with over 5 years working experience of cardiac MR imaging. The participating centers need to be equipped with MRI scan on 1.5 T or 3.0 T platforms with dedicated cardiac receiver coils. During imaging, the patients will be kept in supine position. A standard electrocardiographic triggering device will be used for heart rate triggering and monitoring.

A sample protocol is provided for all modalities (Figure 2). The participating sites will be allowed to use their own acquisition protocols, provided that standard cine, late gadolinium enhancement (LGE) and mapping images should be acquired according to the current practice guidelines. In the sample protocol, a balanced steady state free precession sequence (bSSFP) will be used to acquire continuous short‐axis (SAX) slices encompassing the whole LV, standard two‐, three‐, and four‐chamber cine images during repeated breath holds. After then, a dose of 0.1 mmol/kg Gadolinium will be injected at a flow rate of 2.5–3.0 ml/s. LGE images will be acquired 10–15 min after contrast administration using a phase‐sensitive inversion recovery sequence. Pre‐contrast T1 mapping and T2 mapping will be acquired, and a repeat MOLLI T1 mapping will be performed after LGE for the post‐T1 mapping.

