### Endpoints definition

2.8

The main endpoint is selected to characterize the effect of ARNI on ventricular remodeling as compared to ACEI. Based on the results from previous studies on LV remodeling, change of the indexed LV mass (Δ LVmassi) from baseline to 6‐month follow‐up on CMR is set to be the measurement for the primary outcome.^22^

Similarly, other secondary CMR outcomes include other remodeling parameters from baseline to 6‐month follow‐up (Δ left ventricular ejection fraction [LVEF], Δ LVEDV, Δ LVESV), peak LV strains (global radial peak strain, global circumferential peak strain, and global longitudinal peak strain), strain rates (global radial peak strain rate, global circumferential peak strain rate, and global longitudinal peak strain rate), infarction size as measured through LGE, presence of microvascular obstruction (MVO) on LGE, presence of iron load evaluated on T2* images, T1 mapping, and T2 mapping indexes at the 6‐month CMR.

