### Statistical analysis

2.11

Primary trial analyses will be based on the modified intention to treat (ITT) population in which patients without a measurement of primary outcome will be excluded and additional analyses will also be performed on the per protocol population (PP). Considering that patients who received implantation of implantable cardioverter defibrillator (ICD) or cardiac resynchronization therapy (CRT) within 6 months will be unable to receive the second MRI examination, ITT population will consist of all randomized patients with valid outcome measurement. PP population is a subset of the ITT population in which patients with major protocol deviations will be excluded. Protocol deviations will be defined in the statistical analysis plan.

For the analysis of the primary outcome (change of the indexed LV mass (Δ LVmassi) from baseline to 6‐month follow‐up on CMR), a linear regression model will be employed with treatment as the study variable and baseline measurement of indexed LV mass as a covariate. In addition, adjusted linear model analysis will be performed with the pre‐specified covariates (LVEF, anterior infarction, MVD, presence of MVO on LGE, diabetes, hypertension, and the use of SGLT2i) measured at baseline being added into the above linear model. The crude and adjusted mean differences in the primary outcome together with its 95% confidence intervals at 6‐months will be derived from the linear models. In addition, subgroup analysis of primary endpoint will be performed on the above pre‐specified covariates.

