Analysis of secondary continuous outcomes with single follow‐up measurement will be done in a similar fashion as the primary endpoint analysis. Analysis of secondary continuous outcomes with repeated follow‐up measurement will be performed using a linear mixed model with treatment visit, interaction between treatment and visit as fixed effects, the baseline value of the outcome as covariate if it is available, and subject as random effects. The analysis of binary outcomes will also use a generalized linear/mixed model depending on whether there will be a repeated measurement. Odds ratios with their 95% confidence intervals will be derived from the generalized linear/mixed model analysis. For the analysis of time‐to‐event outcome, Kaplan–Meier curves will be presented and compared by log rank test by treatment group, and hazard ratio and its 95% CI will be calculated using Cox regression model with the treatment arm as the study variable.

Missing primary outcome and secondary outcomes with a single measurement will not be imputed but missing secondary outcomes with repeated measurements will be imputed in sensitivity analysis using the last observation carried forward strategy. Missing baseline covariates will be imputed using simple imputation methods in the covariate adjusted analysis based on the covariate distributions in the sample. For a continuous variable, missing values will be imputed from random values from a normal distribution with mean and SD calculated from the available sample. For a categorical variable, missing values will be imputed from random values from a uniform distribution with probabilities *P*
_
*1*
_, *P*
_
*2*
_,…, and *P*
_
*k*
_ from the sample. Seed for the imputation is set as the date of data analysis (e.g., 270 521).

The study is powered to make a single comparison in the primary outcome at 6 months only and other comparisons are exploratory in nature. Therefore, there is no multiplicity issue. All analyses will be described in detail in the statistical analysis plan. SAS 9.4 will be employed for the statistical analyses.

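### The planned models for the exploratory T1 and T2 mapping outcomes have no field-strength term although 1.5 T and 3.0 T scanners are both allowed: a small, almost free gain in precision

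*Protocol article*

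**What the plan says.** Section 2.5 (Imaging study and analysis) requires participating centres to be "equipped with MRI scan on 1.5 T or 3.0 T platforms". It adds that "The participating sites will be allowed to use their own acquisition protocols", provided that cine, late enhancement and mapping images follow current practice guidelines. In the sample protocol, "Pre‐contrast T1 mapping and T2 mapping will be acquired, and a repeat MOLLI T1 mapping will be performed after LGE".

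Section 2.8 (Endpoints definition) lists among the secondary outcomes "T1 mapping, and T2 mapping indexes at the 6‐month CMR". It gives no unit, derivation or normalisation.

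Section 2.11 (Statistical analysis) sets the model for this class of outcome: "Analysis of secondary continuous outcomes with single follow‐up measurement will be done in a similar fashion as the primary endpoint analysis". For the primary outcome, "a linear regression model will be employed with treatment as the study variable and baseline measurement of indexed LV mass as a covariate". An adjusted version adds baseline LVEF, anterior infarction, multivessel disease, microvascular obstruction, diabetes, hypertension and SGLT2 inhibitor use. Neither version contains field strength, scanner or centre, although section 2.3 stratifies randomisation by centre. The same section calls all comparisons other than the primary one exploratory and defers detail to the statistical analysis plan.

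**The concern.** The model was written for indexed LV mass, a geometric quantity that means the same on any magnet. T1 and T2 are relaxation times, and these depend on field strength. That is general MR physics and not a statement in the article, so the size of the dependence is treated below as an assumption. If the indexes are analysed in milliseconds, two patients with identical myocardium have different values at 1.5 T and 3.0 T, even when each patient is scanned on the same magnet both times.

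The baseline value carries much of this offset, but not all of it. One regression slope has to serve two relations: between fields, where follow-up tracks baseline with a slope near 1, and within a field, where the slope is lower. The mismatch goes into the residual.

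What is at stake is precision on the mapping outcomes. The Discussion presents tissue characterisation as a way to understand how the drug acts, so a modest tissue effect could be harder to see than it need be.

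**Working it through.** **The plan's own figure.** The only sample size stated is for indexed LV mass (section 2.10): difference 4.81, SD 16.65, at least 80% power. With two-sided alpha 0.05 (assumed), n per arm = 2 × (1.960 + 0.842)² × (16.65/4.81)² ≈ 188.1, so 189 against the stated 188. Power at 188 is 79.98%. The figure reproduces, and the present point does not touch it. No figure is given for mapping.

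**Inputs, all assumed.** D is the offset between fields in within-field SDs. An SD of 50 ms and an offset of 100 to 200 ms for native T1 give D = 2 to 4. The within-field correlation between baseline and 6 months is ρ = 0.3 to 0.7. The share of patients at 3.0 T is p = 0.3 to 0.7. Each patient has the same field strength at both visits.

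**Formula.** Set the within-field variance to 1 and let V = p(1 − p)D².
- Residual variance with treatment and baseline only: (V + 1) − (V + ρ)²/(V + 1).
- Residual variance with a field-strength term added: 1 − ρ².
- The ratio simplifies to (2V + 1 + ρ) / [(V + 1)(1 + ρ)]. It is 1 when D = 0 and cannot exceed 2/(1 + ρ).

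**Ends of the range.**
- D = 2, p = 0.3, ρ = 0.7: V = 0.84, ratio = 3.38/3.128 = 1.08.
- D = 4, p = 0.5, ρ = 0.3: V = 4, ratio = 9.3/6.5 = 1.43.

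This equals discarding 1 − 1/1.08 ≈ 7% to 1 − 1/1.43 ≈ 30% of the patients.

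**Ratios at p = 0.5.**

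| D | ρ = 0.3 | ρ = 0.5 | ρ = 0.7 |
|---|---|---|---|
| 1 | 1.11 | 1.07 | 1.04 |
| 2 | 1.27 | 1.17 | 1.09 |
| 4 | 1.43 | 1.27 | 1.14 |
| ceiling | 1.54 | 1.33 | 1.18 |

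Without any baseline covariate the ratio would be 1 + V, that is 2 at D = 2 and 5 at D = 4 (p = 0.5). The baseline value therefore already removes most of the offset.

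**Power.** At ρ = 0.5 and p = 0.5, a contrast with 80% power when field strength is in the model has 74% (D = 2) to 70% (D = 4) without it. In milliseconds, with 376 patients and an assumed true difference of 15 ms, simulated standard errors were 4.96 without the term and 4.48 with it (offset 150 ms, ρ = 0.5): power 86% against 92%. For offset 200 ms and ρ = 0.3 they were 5.89 and 4.94: power 72% against 86%.

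**Bias.** A simulation used 376 patients in 20 centres, half of them at 3.0 T, with centre-stratified blocks (block size 4 assumed) and ρ = 0.5. Without the field term the mean estimate was 0.252 (D = 2) and 0.250 (D = 4) against a true 0.250. Type I error was 0.039 and 0.045, so it was not inflated.

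**Change of field between visits.** The article does not require the same scanner twice. If 10% of patients change field strength (p = 0.5, ρ = 0.5), the residual variance is about 1.5 times (D = 2) to 3.0 times (D = 4) the within-field value 1 − ρ².

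**The case against.** The strongest reply is that this is detail for the statistical analysis plan. The article gives the mapping outcomes only a general sentence, a similar approach need not mean an identical covariate list, and scaling may be fixed in that plan or by the core laboratory. This stands in part: the article does not exclude a scanner term. But it does name a model for these outcomes and lists the covariates, and a plan that followed it would leave field strength out.

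A reader might also infer more than the documents support:
- *That mapping values are pooled in raw milliseconds.* The article speaks only of indexes and acquires T1 before and after contrast, so a derived or normalised measure is possible. The point is conditional on this.
- *That the model holds only treatment and baseline.* An adjusted version with seven covariates is also planned. None of them stands in for field strength.
- *That the comparison between arms is biased or has no common scale.* Only the mean level in each arm depends on its mix of field strengths. Randomisation is 1:1 and stratified by centre, and the difference between arms remains estimable and unbiased, given a treatment effect of the same size at both fields.

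Two further objections stand in full. Every input to the size is assumed and the figures are for native T1; no calculation was made for T2 or post-contrast T1. And the outcomes are exploratory, so no powered conclusion depends on them.

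**Conclusion.** The point holds as a low-severity improvement. The article allows two field strengths and site-specific sequences, and the models it names for the mapping outcomes account for neither. If the indexes are not normalised, residual variance for native T1 is about 8 to 43% larger than necessary under the ranges assumed above. The excess is smaller if the offset is small relative to the SD (4 to 11% at one SD and p = 0.5) and larger if some patients change field strength between visits. The loss is one of precision only: there is no bias and no inflation of type I error, and the primary endpoint and its sample size are unaffected.

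**What to change.** In section 2.11, state that the linear models for T1 and T2 mapping indexes, crude and adjusted, include field strength as a fixed effect, and mapping sequence where it differs. Where a patient's two scans were made at different field strengths, both should be represented in the model. Report mapping means by arm separately for 1.5 T and 3.0 T beside the pooled adjusted difference. If the indexes are to be normalised, say how. Centring the baseline value within field strength is not needed: with a common slope and field strength in the model, it leaves the treatment estimate unchanged.

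The cost is a sentence of text and one or two degrees of freedom. Field strength and sequence should be recorded with the images that section 2.5 already sends to the core laboratory. No extra patients or scans are needed.
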